[figure not shown]

## 1. Summary

In its 2015 revision of the global guidelines for HIV care and treatment, the World Health Organization called for initiating lifelong antiretroviral treatment (ART) for all patients testing positive for HIV, regardless of CD4 cell count. As countries adopt the new recommendation, known as “treat all,” millions of additional patients are becoming eligible for ART worldwide. In sub-Saharan Africa, where most of these patients are located, studies continue to document high losses of treatment-eligible patients from care before they receive their first dose of antiretroviral medications (ARVs). Among facility-level reasons for these losses are treatment initiation protocols that require multiple clinic visits and long waiting times before a patient who tests positive for HIV is dispensed an initial supply of medications. Simpler, more efficient, accelerated algorithms for ART initiation will be needed if “treat all” is to realize the benefits expected.

At a technical consultation convened in October 2015, participants proposed a simplified clinical algorithm to screen patients for eligibility for immediate ART initiation at a patient’s first clinic visit, without the use of point-of-care laboratory test technologies. The Simplified Algorithm for Treatment Eligibility (SLATE) uses four screens to assess whether a patient is eligible for immediate (same-day) treatment initiation: i) symptom report, ii) medical history, iii) readiness assessment, and iv) brief physical examination. SLATE is a pragmatic, individually randomized evaluation to determine the effectiveness of the algorithm in increasing ART initiation, compared to standard care, among non-pregnant adult patients. A total of approximately 960 HIV-infected adult patients not yet on ART will be enrolled during a routine clinic visit and randomized to receive the intervention or standard care. Patients in the intervention arm will be administered the SLATE screens; those found eligible under the algorithm will be offered immediate treatment initiation, while those who are not eligible will be referred for standard clinic care. Patients in the standard arm will be referred for ART initiation under standard clinic procedures. All care after the initial visit will be by the clinic under standard of care. The study will be conducted at three healthcare facilities (clinics) in each of two countries, South Africa and Kenya. If successful, SLATE will offer a standardized approach to collecting and interpreting a minimum set of patient data that will avoid delaying treatment initiation for the majority of patients who are eligible for immediate ART, while deferring initiation in the minority who should not start immediately.

### **3. Background**

#### *3a. Context: New guidelines for HIV treatment eligibility*

In its 2015 revision of the global guidelines for HIV care and treatment, the World Health Organization called for initiating lifelong antiretroviral treatment (ART) for all patients testing positive for HIV, regardless of CD4 cell count. This revision followed a series of increases in the global guidelines in the threshold for initiating ART, from a CD4 count of  $\leq 200$  cells/mm^3 prior to 2010, to 350 until 2013, to 500 at present. In its recommendation, the WHO cites three anticipated benefits from this approach, which is referred to as “treat all” (alternatively, “test and treat” or “test and start”): reduced morbidity among HIV-infected patients; reduced risk of transmission from HIV-infected individuals to their partners; and “increases in ART uptake and linkage to care, reduction in the time between HIV diagnosis and ART initiation regardless of baseline CD4 cell count and an increase in the median CD4 value at ART initiation.” A recent analysis concluded that future reductions in HIV-related mortality in sub-Saharan Africa will derive largely from this last benefit, rather than from the first two.

Multiple African countries—including South Africa and Kenya, where the proposed study will take place—have already announced their plans to adopt the new guidelines, and it is clear that the trend globally is toward offering ART to all. As this happens, national HIV programs will face the challenge of

initiating individuals newly diagnosed as HIV-infected on ART as efficiently as possible, while ensuring that retention on ART and patient welfare are not jeopardized by the initiation process.

### *3b. The problem: loss to follow up before treatment initiation*

Studies from throughout sub-Saharan Africa continue to document high losses of treatment-eligible patients from care before they receive their first dose of ARVs. A systematic review of the literature on pre-ART retention in care found that roughly one third of adult patients in sub-Saharan Africa who had already been determined eligible for ART did not start ART within the studies' follow-up periods. If those diagnosed with HIV but not assessed for treatment eligibility had been added, this proportion would have been far higher. Reasons for this include a wide range of facility- and patient-level barriers to initiation. Among facility-level barriers are clinic inaccessibility and inefficiency and initiation protocols designed for the convenience of providers rather than patients. These barriers manifest themselves as multiple required visits, long waiting times, stock outs of supplies, staff absences, and poor communication between staff and patients. Eliminating the eligibility threshold under a "treat all" policy is not likely to solve these problems, as clinics become even more crowded with newly-eligible patients. Simpler, more efficient, accelerated algorithms for ART initiation will be needed if "treat all" is to realize the benefits expected.

In an earlier clinical trial in South Africa (RapIT, H-31880), we demonstrated that same-day treatment initiation, in which all the steps required for ART initiation are performed in sequence during a single clinic visit, significantly increased the proportion of eligible patients started on treatment (RR 1.36, 95% CI 1.24–1.49) and the proportion virally suppressed six months later (RR 1.26, 95% CI 1.05–1.50). The RapIT trial was premised on the notion that standard of care treatment initiation, which in South Africa required 5 or 6 clinic visits over a 1-2 month period, created a burden on patients that deterred many from completing the process. In addition to delaying the start of treatment, each clinic visit entailed transport costs and time, many hours of waiting time in the clinic, and possibly lost wages, child care, and other costs for the patient. The results of the study indicate that accelerating the initiation process does overcome these barriers; in the intervention arm of the study, 75% of study subjects started treatment on the same day as study enrollment, and nearly all the rest within one month. The study demonstrated that it is possible to initiate nearly 100% of eligible patients, and eliminate loss to follow up at this point in the care cascade.

Although RapIT and other studies have shown that the vast majority of patients presenting for HIV care at clinics in Africa can safely start ART on the same day, without delay, there are still patients for whom a delay is necessary. These reasons include:

- Tuberculosis (TB): To minimize the risk of immune reconstitution inflammatory syndrome (IRIS), two weeks of TB treatment is recommended for patients presenting with active TB before ART is started.
- Cryptococcal meningitis (CM): Patients with low CD4 counts should be screened for cryptococcal antigen (CrAg) and given presumptive treatment for CM before ART is started, again to minimize the risk of IRIS.
- Other clinical conditions: HIV patients present with a range of symptoms and conditions that may lead a clinician to decide to delay ART while further investigations or treatment are completed.
- Patient history: Patients who previously defaulted from ART or have a history predicting non-adherence, such as substance abuse, may require additional support before starting ART.
- Patient readiness: Finally, some patients may feel that they are not ready to start treatment on the same day and choose for themselves to delay initiation.

The RapIT trial used multiple rapid, point-of-care laboratory test instruments to generate the laboratory data required for ART initiation in South Africa. The generalizability of its findings is thus limited by the need for expensive equipment that will not be feasible to maintain in most primary healthcare clinics in the region. RapIT also excluded many ART-eligible patients on the basis of clinical trial-specific exclusion criteria that would not apply in a routine care setting. What is needed now is a way to assess eligibility for immediate treatment initiation that is broadly applicable to nearly all patients and does not require either point-of-care laboratory instruments or delays for laboratory results to be received, while screening out patients who should not start treatment immediately for clinical or personal reasons.

*3c. Proposed solution: a standardized clinical algorithm for determining eligibility for immediate treatment initiation*

In October 2015, the investigators convened a technical consultation of experts in the field to discuss models for accelerating treatment initiation. Participants in that meeting proposed a simplified clinical algorithm to screen patients for eligibility for immediate ART initiation without the use of point-of-care technologies. The simplified algorithm, abbreviated “SLATE,” is illustrated in Figure 1.

**Figure 1. SLATE algorithm**

[figure not shown]

As shown in Figure 1, the SLATE algorithm uses four screens to assess whether a patient is eligible for immediate (same-day) treatment initiation. Each of the screens is intended to identify specific reasons that a patient might *not* be eligible, including current symptoms of opportunistic infections, previous experiences or behaviors that indicate a need for additional treatment readiness or adherence support, and the patient's own concerns about starting treatment. The algorithm captures all components of treatment eligibility screening currently used in routine care in the study countries with the exception of pre-initiation laboratory results. It follows national guidelines for detection of co-morbidities, which vary by country; some countries call for a CrAg test for patients with CD4 counts < 100, for example, while others do not conduct routine CrAg screening.

The purpose of the SLATE algorithm is to create a standardized approach to collecting and interpreting a minimum set of patient data that will avoid delaying treatment initiation for the majority of patients who are eligible for immediate ART, while deferring initiation in the minority who should not start immediately. If successful, it is expected to increase overall uptake of ART and viral suppression in the population of HIV-infected adults eligible for ART in sub-Saharan Africa.

#### **4. Objectives**

The SLATE study is a pragmatic, individually randomized evaluation to determine the effectiveness of the SLATE algorithm in increasing ART initiation, compared to standard care, among non-pregnant adult patients. Patients will be individually randomized to either an intervention arm, in which the SLATE algorithm will be implemented, or a standard arm, in which they will receive standard treatment initiation.

##### *4a. Primary objectives*

The primary objectives of this study are to:

1. Compare the proportion of study-eligible patients who initiate ART within 28 days of study enrollment between HIV-infected patients offered immediate ART initiation under the SLATE algorithm and patients offered standard ART initiation.
2. Compare the proportion of study-eligible patients who initiate ART and are alive, in care, and retained on ART by eight months after study enrollment between HIV-infected patients offered immediate ART initiation under the SLATE algorithm and patients offered standard ART initiation.

##### *4b. Secondary objectives*

The secondary objectives of this study are to:

3. Compare the proportion of study-eligible patients who initiate ART within 14 days of study enrollment between HIV-infected patients offered immediate ART initiation under the SLATE algorithm and patients offered standard ART initiation.
4. At sites where viral load data are available, compare the proportion of study-eligible patients who initiate ART and are virally suppressed eight months after having an HIV test or enrolling in HIV care
5. Compare the proportion of study-eligible patients who initiate ART and are alive, in care, and retained on ART by 14 months and 16 months after study enrollment between HIV-infected patients

offered immediate ART initiation under the SLATE algorithm and patients offered standard ART initiation.

6. Estimate the proportion of HIV-positive patients presenting at study clinics and not yet on ART who are eligible or ineligible for immediate initiation using SLATE algorithm criteria.
7. Describe reasons for ineligibility for immediate initiation, among those found ineligible in the intervention arm.
8. Estimate average time interval in days between study enrollment and ART initiation for each study arm.
9. Describe self-reported patient preferences on the speed and timing of ART initiation.
10. Estimate costs to patients of implementing the SLATE algorithm, compared to standard care.
11. Estimate costs to providers of implementing the SLATE algorithm, compared to standard care.

## **5. Study Design**

### *5a. Overview*

The study will be an individually randomized evaluation that will collect data from consented study subjects using questionnaires, a brief physical examination, a venous blood draw where not already done under routine care, and review of routine medical records. Patients randomized to the intervention arm will be initiated on ART if eligible under SLATE or referred for standard care if not eligible under SLATE. Health facility information that does not pertain to human subjects (e.g. unit costs) will also be collected. Figure 2 summarizes study design and procedures.

Figure 2. SLATE study procedures

[figure not shown]

### 5b. Study sites

The study will be conducted at three high-volume, public sector clinics in each study country. We selected sites that have both a relatively high volume of potentially study-eligible patients, to reduce the time required for enrollment, and have service delivery infrastructure and staff that are typical of the public sector, so that results will be broadly generalizable within each country.

Sites were selected in collaboration with local study teams and in consultation with government health authorities in each area. A letter confirming government authorization for each site to participate in this study will be submitted to the BU and local IRBs prior to study enrollment at that site.

The proposed sites in each country are:

South Africa:

- OR Tambo Primary Health Clinic, City of Johannesburg
- Alexandra Community Health Centre, City of Johannesburg
- Jabulani Dumani Community Health Centre, Ekurhuleni Metro

Kenya:

- Kericho County Referral Hospital, Kericho
- Kapsabet County Referral Hospital, Kapsabet
- Kombewa County Hospital, Kombewa

### *5c. Study population*

The study population will be all non-pregnant HIV-infected adults who are not yet on antiretroviral therapy.

#### *Inclusion criteria:*

- Adult patients ( $\geq 18$  years) (initiating children on ART is likely to require additional information, making the SLATE algorithm less applicable to pediatric populations)
- Confirmed HIV-positive test result at any time (may have been diagnosed previously)
- Not currently on ART (three-drug combination)
- Presented at the study clinic for any HIV-related reason, including an HIV test, pre-ART monitoring, or ART initiation

#### *Exclusion criteria:*

- Pregnant (pregnancy is an exclusion criterion because treatment guidelines for pregnant women differ from those for non-pregnant adults; most pregnant women are diagnosed with HIV and initiated on ART in antenatal clinics, not general adult HIV clinics)
- Not intending to return to this clinic for further HIV care in the coming year (i.e. intends to seek further care somewhere else)
- Not physically, mentally, or emotionally able to participate in the study, in the opinion of the investigators or study staff
- Not willing or able to provide written informed consent to participate in the study
- Previously enrolled in the same study

All the study countries have adopted a policy of “treat all” or “test and treat”, so that all SLATE study subjects will also be eligible for ART under national guidelines. Although implementation of this policy may not be complete and may vary by site, we will enroll all patients who would be eligible under expected treat all guidelines regardless of actual clinic-specific practice at the time of the study. This will

ensure that the SLATE study can generate information for a future in which “treat all” is the standard in most places.

Patients will be followed passively through medical record review for up to 16 months after study enrollment.

## **6. Enrollment and Preparation**

### *6a. Pre-screening*

Patients presenting at a study clinic who are HIV-infected but not yet on ART will be eligible for study pre-screening. This includes patients diagnosed earlier and patients newly diagnosed on the same day. At each study site, the site’s staff (counselors, clerks, and clinical staff, as appropriate to each site) will inform potentially eligible patients about the study at visit registration, which will be defined as the patient’s first point of contact with clinic staff upon arriving at the clinic. Patients who express willingness to learn more about the study will be referred to a study assistant for screening and consent. Patients will be assured that they will not “lose their place” in the clinic queue by agreeing to referral to the study assistant; upon completion of interaction with study staff, the study assistant will escort patients who do not want to participate or who were randomized to standard care to return to their original place in the queue (or front of the line in case their place was lost) to continue with their routine clinic visit.

Where feasible, clinic staff who refer patients to the study assistant will be asked to complete one row in a pre-screening logbook (Appendix 1) for each patient they inform about the study, to allow the study to collect aggregate statistics about the overall patient population and compare it to the screened population. Fields that will be recorded in this logbook are date, sex, age in years, and primary reason for clinic visit (HIV test, CD4 count, pre-ART monitoring, adherence education session, ART initiation). No identifiers of any kind will be collected in this logbook, which is intended to provide only aggregate information. We anticipate that use of the logbook will be feasible at some study sites and some first points of contact at those sites but may not be feasible at others, if clinic staff are too busy or do not remain in a fixed location in the clinic. Where the logbook cannot be used, clinic staff will follow the same procedures for information patients about the study, but no record will be kept. Data analysis requiring pre-screening data will be limited to sites where the logbook is used.

### *6b. Screening*

Upon referral to the study assistant, patients will receive a more complete description of the study, including the details of why it is being done, study procedures, and the need for written informed consent. They will be assured that participation is voluntary and that they can withdraw from the study at any time, without affecting the quality of care provided by the site. They will also be offered the opportunity to ask questions. If the study assistant concludes that all other inclusion/exclusion criteria have been met, patients will then be asked to provide written informed consent to participate, as described below. The study assistant will complete a screening form (Appendix 2) to confirm study eligibility for each patient screened. The screening form will not collect any identifiable information pertaining to individual patients prior to receipt of written informed consent.

Patients will be screened consecutively, as they arrive at the study site. Due to the volume limitations of study staff, however, recruitment may be halted during intervals when the study assistant and/or study

clinician are already busy. We anticipate that clinical data collection will take no more than 30 minutes per patient, allowing us to enroll and collect data from roughly 8-10 patients per day using a single study clinician per site.

#### *6c. Consent*

Written informed consent will be obtained from all study participants after screening and prior to study enrollment. The study information sheet and consent form (Appendix 3) will be translated into local languages most commonly spoken by patients at the study sites. Translated consent documents and attestation of consent accuracy will be submitted to the BUMC IRB and local IRB prior to use with any study subjects. Potential subjects will be asked if they would prefer to read the information sheet or have it read to them by the study assistant and will be given the opportunity to ask questions about the study. Those who provide written informed consent will be enrolled. Those who refuse consent will be referred back to the clinic staff to complete their routine visit, and the study assistant will indicate the refusal on the screening form.

#### *6d. Pregnancy test*

Because SLATE is not intended for pregnant women, we will conduct a rapid pregnancy test for female patients following consent. Women who have already reported being pregnant will have been screened out prior to consent; the pregnancy test will identify those who were not aware of being pregnant. Patients who have a positive pregnancy test will be withdrawn from the study at this time and escorted to the clinic registration desk to begin antenatal care and PMTCT.

#### *6e. Questionnaire*

The study assistant will administer a short questionnaire documenting the subject's basic demographic and socioeconomic characteristics, costs incurred per clinic visit, and preferences regarding ART initiation. As the questionnaire elicits only simple responses and will be completed by the study assistant not the subject, we do not intend to translate the questionnaire itself into subjects' first languages. Instead, for subjects who do not speak English, the assistant will ask the questions in one of the commonly-understood languages used by the study population, and then record the answers in English on the questionnaire. The questionnaire is included in the study case report form in the appendix to this protocol.

#### *6f. Randomization*

After the questionnaire has been completed, patients will be randomized to the intervention or standard groups of the study. Randomization envelopes will be generated in blocks of 6 and kept at the study sites. For each enrolled patient, the study assistant will open the next envelope in sequential order, read the randomization group, and record it on the case report form. The study assistant will then inform the patient of the randomization assignment.

Following randomization, standard group patients will be escorted to the clinic registration desk to resume their routine clinic visit. The study assistant will repeat the explanation of next steps in the study, which are limited to review of medical records by the study team, provide study payment as described below, and thank them for their willingness to participate in the study. The study team will have no further personal contact with patients in the standard group.

The study assistant will introduce intervention group patients to the study clinician for algorithm data collection. The study clinician will be a nurse, medical officer, or clinical officer at the same level as the individual responsible for ART initiation under standard care at the study site.

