## **11. Sample Size**

Using results of the RapIT randomized trial we recently conducted in South Africa, we estimate that 65% of treatment-eligible patients will be initiated on antiretroviral therapy and retained on ART in the standard group, and we consider an increase to 80% to be programmatically important. Using an  $\alpha$  of 0.05, power of 90%, 1:1 randomization, and an uncorrected Fisher's exact test, this requires a minimum sample size of 197 patients per group, which we will increase to a maximum of 240 per group to ensure sufficient power if patients withdraw or are found ineligible after consent, or 480 per country.

In addition, in South Africa only, we would like to be able to compare between study sites the proportions of patients in the intervention group who screen in and screen out of the SLATE algorithm. Based on early enrollment, we expect the proportion screening in to be a maximum of 67%, which we will conservatively reduce to 60%. We expect the proportion screening in to be a minimum of 32%, which we will conservatively increase to 35%. With an  $\alpha$  of 0.05 and power of 90%, we estimate that we will need to enroll a minimum of 79 patients in the intervention arm per site, or a minimum of 158 participants in both arms per site. In order to maintain constant enrollment periods at all three sites in South Africa, we will continue to enroll until the slowest site has reached a minimum of 158. We anticipate that total enrollment at that point will be a maximum of 660 participants in South Africa.

The sample size will thus be a maximum of 480 in Kenya and 660 in South Africa, or a maximum of 1140 for the two-country study.

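### A single block size of 6, printed in the protocol, lets the assistant who screens, consents and opens the envelopes know up to a quarter of allocations in advance

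*Protocol*

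**What the plan says.** Protocol section 6f fixes the block size: "Randomization envelopes will be generated in blocks of 6 and kept at the study sites". Opening them falls to a single role at the site: "the study assistant will open the next envelope in sequential order, read the randomization group, and record it on the case report form". That person also tells the patient which arm was drawn, so the assignment is open to both. Section 11 gives the ratio: "power of 90%, 1:1 randomization, and an uncorrected Fisher's exact test". A block of 6 therefore holds three envelopes per arm.

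The same role acts earlier in the pathway. Section 6b makes consent depend on the assistant's judgement of eligibility: "If the study assistant concludes that all other inclusion/exclusion criteria have been met". Section 13e has a trained study assistant seek consent.

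Three provisions leave room for judgement before the envelope is opened:

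- Section 5c excludes a patient who is "Not physically, mentally, or emotionally able to participate in the study, in the opinion of the investigators or study staff".
- Section 13a (emotional distress) tells study staff to end or put off enrollment when a patient seems distraught.
- Section 6b requires consecutive screening, but lets workload interrupt it ("recruitment may be halted during intervals when the study assistant and/or study"); the condition is that one or both of these staff have no free time.

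Section 12b makes the crude comparison of proportions the primary analysis and brings in an adjusted model only if important chance imbalances appear.

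**The concern.** Allocation is not masked from the person who recruits, and the one block size can be read in the protocol. After each envelope that person knows the running tally. Late in a block the tally can fix the next arm before the next patient has been approached.

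Both primary outcomes, starting ART within 28 days and being retained at eight months, plausibly depend on how ready or how unwell a patient is. An assistant who knows the next arm could, without any bad faith, apply the opinion-based exclusion or the distress rule a little differently. There is also a practical pull. Section 6b plans on one study clinician per site, and section 7a expects up to 30 minutes of clinician time on average per intervention patient. A standard-arm patient needs none.

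Selection at this stage comes before outcome measurement, so record-based outcomes do not protect against it. The traits most likely to drive it are also poorly measured in both arms. Under section 9d the symptom, history, examination and readiness forms are completed only in the intervention arm. Section 9e adds CD4 count, WHO stage and any TB symptom screen for all subjects, but only as found in routine records.

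**Working it through.** The protocol states no predictability figure, so there is none to reproduce.

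**Inputs.** Block size 6 (section 6f). Ratio 1:1 (section 11), so 3 + 3 per block. Maximum enrollment 1140 (section 11); about 960 (section 1). Assumed: the assistant knows the block size and tracks one sequence per site.

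**Certain allocations.** An allocation is certain once the other arm's three places are used. There are C(6,3) = 20 equally likely orderings. The number of certain allocations is one in 12 orderings (60%), two in 6 (30%) and three in 2 (10%).

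- Expected number: (12×1 + 6×2 + 2×3)/20 = 30/20 = 1.5 per block.
- Share: 1.5/6 = 25%. The closed form for block size 2m is 1/(m+1); with m = 3 this is 1/4.
- Count: 0.25 × 1140 = 285; 0.25 × 960 = 240.

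Every block has at least one certain allocation.

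**Best guessing.** Guess the arm that is behind, or toss a coin when tied. The chance of being right at positions 1 to 6 is 0.5, 0.6, 0.6, 0.7, 0.7 and 1.0. The sum is 4.1, and 4.1/6 = 68.3%, against 50% under simple randomization.

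**Varying sizes (4, 6 and 8 assumed, drawn with equal probability).**

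- Certainty: in a simulation of 100,000 allocations, an observer who knew the set of sizes but not the size in use was certain of about 2.3%.
- Guessing: every block ends balanced, so the arm behind overall is the arm behind in the block, whatever its size. Expected correct guesses are 2.833 of 4, 4.1 of 6 and 5.329 of 8. Together (2.833 + 4.1 + 5.329)/18 = 12.262/18 = 68.1%.
- A longer fixed block does less for certainty: 20% at size 8 and 14.3% at size 12.

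**What selection could do (assumption, not an estimate).** Suppose patients entering a known intervention place have a success chance d points above average, and those entering a known standard place d points below. On average a quarter of each arm is affected, so the arm difference shifts by 0.25d + 0.25d = 0.5d. With d = 0, 5 and 10 the shift is 0, 2.5 and 5 points. The target contrast in section 11 is 80% − 65% = 15 points.

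**The case against.** The case against is substantial, and most of it stands as a limit on the point.

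- **Pausing.** A reader might infer that the assistant is free to pause recruitment before an unwelcome envelope. Section 6b does not support that: screening is consecutive and halts are tied to staff being busy. The envelope also comes after consent, pregnancy test and questionnaire. The halt is at most an indirect route; the opinion-based exclusion and the distress rule are the main ones.
- **Partial safeguards.** The screening form records each criterion and the reason for ineligibility (section 9c). Where feasible, a logbook lets enrolled patients be compared with the clinic population (section 9b). The formal screens follow randomization and are done by the clinician, so while screening the assistant has only informal impressions. These make steering harder and partly visible. They do not stop anticipation of the next arm.
- **Adjustment.** Section 12b does provide for an adjusted model. It addresses measured imbalance, not unmeasured selection.
- **Unstated premises.** The protocol does not say that assistants know the block size or follow block boundaries, nor that the lists are made on site. No fault in where the lists are generated can be read from it.
- **The remedy.** A reader might expect varying block sizes to cure guessing as well as certainty. The figures show that they do not.

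**Conclusion.** The point holds as an avoidable risk. A fixed, published block size of 6, with one unmasked role covering eligibility, consent and envelope opening, makes an expected 25% of allocations knowable with certainty. This rests on two assumptions: the assistant knows the size and tracks the tally, and each site runs its own sequence. Nothing in the protocol contradicts either.

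The figure of 285 is an upper bound, at maximum enrollment. It counts predictable allocations, not biased ones. A reader might infer that the comparison is already biased, or that 285 patients are compromised. The protocol supports neither: it contains no evidence that anyone acted on a prediction, and the direction and size of any effect are unknown. The 25% is firm given the assumptions; the consequence for the treatment contrast is not estimated.

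**What to change.** For envelopes not yet opened, regenerate the site lists with randomly varying block sizes, for example 4, 6 and 8. Withhold the sizes from site staff, and remove the block size from section 6f in the protocol copy they hold. Section 11 refers to early enrollment, so envelopes already opened are beyond reach.

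The amendment should state the benefit accurately: certain allocations fall from 25% to about 2%, even for someone who knows the set of sizes, while best-guess success stays near 68%.

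The cost is reprinting envelopes, a short amendment and slightly more possible imbalance. The largest possible difference between arms within a site sequence is half the block, so it rises from 3 patients to 4.
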